### Sample size

Sample size calculation was performed using STATA version 8.2. Based on a power of 0.80 with a two-sided α of 0.05 and assuming a mean standardized effect size of (Cohen’s *d*) 0.45 a total of 154 participants are needed, 77 participants in the experimental group and 77 participants in the waitlist control group. Due to a lack of studies in this area, the standardized effect size used to calculate the sample size for this study is not based on previous studies or a pilot study. As an alternative, a moderate effect size has been estimated.

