### Primary outcome measures

The primary outcomes are i) participants’ ratings on perceived knowledge regarding adolescent suicidality, ii) perceived self-confidence when interacting with suicidal adolescents, and iii) actual knowledge regarding adolescent suicidality.

Since this is the first time e-learning modules on adolescent suicide prevention for gatekeepers have been developed and in order to test their effectiveness, the authors have composed three questionnaires to test the three primary outcomes of this study. This was done in collaboration with adolescent suicide prevention experts involved in this project. In order to test the first and the second primary outcome measures, two short questionnaires have been developed consisting of statements to be endorsed on a three-point Likert scale (0 = disagree, 1 = partially agree, 2 = agree).

The questionnaire measuring perceived knowledge consists of nine items. The first item is a general statement about the overall knowledge of the participants when it comes to adolescent suicide prevention (‘I have sufficient knowledge about the process of recognition, guidance, and referral of suicidal youth’), and the remaining eight statements each capture the essence of one of the eight modules offered. For example, the fifth module focuses on how to engage in a conversation with a suicidal adolescent and the statement measuring the perceived knowledge regarding this module is ‘I have sufficient knowledge to engage in a conversation with a suicidal adolescent’. The questionnaire measuring perceived self-confidence consists of 16 items, each capturing the required skills and attitudes in adolescent suicide prevention which are addressed in the eight modules. Examples of the statements are ‘I can adequately provide first aid to a young person who has attempted suicide’ and ‘I can make a distinction between my duties and those of a therapist’. During the three assessments of the effectiveness study participants receive the same two questionnaires.

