### Statistical analysis plan

The internal consistency reliability of the three questionnaires will be estimated with Cronbach’s alpha and exploratory factor analysis will be used to check for dimensionality.

To test whether the knowledge of gatekeepers and the gatekeeper’s self-confidence increases after gaining access to the website, mean differences of the two groups (experimental and waitlist control) on the three questionnaires will be compared for the three assessment points.

Both analysis of covariance (ANCOVA) and hierarchical linear modeling (HLM) are suitable methods to test the hypotheses of this randomized pre-test, post-test, and follow-up design
[19].

An ANCOVA in which pre-test is used as a covariate can be used to test for group differences from pre-test to post-test, from pre-test to follow-up, and from post-test to follow-up. By including the pre-test as a covariate in the model, more statistical power and statistically accurate confidence intervals of the differences of means between the experimental group and the waitlist control group will be gained
[19]. Missing data will be dealt with by multiple imputation
[20-22]. Alternatively, HLM may be used in which individual growth curves over time are integrated in the model
[19,23]. HLM assumes that data are missing at random
[24].

The data from the evaluation questionnaire, which is only completed by participants from the experimental group, will be analyzed using descriptive statistics. All analyses will be carried out on intention-to-treat sample.

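### Alpha of 0.05 and power of 0.80 fit one unadjusted comparison, but three unranked primary outcomes over several time contrasts have no primary time point, success rule or multiplicity control

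*Protocol article*

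**What the plan says.** **Outcomes.** The section Primary outcome measures lists three primary outcomes: self-rated knowledge, then "perceived self-confidence when interacting with suicidal adolescents, and iii) actual knowledge regarding adolescent suicidality". The authors built "three questionnaires to test the three primary outcomes of this study". None is ranked above the others.

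**Sample size.** One alpha, one power and one effect size are given: "Based on a power of 0.80 with a two-sided α of 0.05", "assuming a mean standardized effect size of" 0.45 (Cohen's d), and hence "a total of 154 participants are needed, 77 participants in the experimental group and 77 participants in the waitlist control group". The section does not say which outcome or time point the calculation is for.

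**Analysis.** Under Statistical analysis plan, "mean differences of the two groups (experimental and waitlist control) on the three questionnaires will be compared for the three assessment points". ANCOVA with the pre-test as covariate is described as suitable for group differences "from pre-test to post-test, from pre-test to follow-up, and from post-test to follow-up". Hierarchical linear modelling is offered as the alternative. The section gives no significance level, order of testing, deciding contrast or multiplicity adjustment.

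**Aim.** Aims and hypotheses, and later the Discussion, pose a single overall question, whether the modules are effective. Knowledge and self-confidence are both expected to improve, but this is not worded as a decision rule.

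**The concern.** An alpha and a power describe a decision. With three primary outcomes and at least two post-baseline time points, the decision has to be defined before the pair means anything for the trial as a whole: which time point counts, and whether one, some or all of the outcomes must be positive. The article fixes the number of participants but not the decision.

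What is at stake is the headline claim. Two of the three primary outcomes are self-ratings, and the Discussion says that none of the questionnaires has been validated. A gain on one self-rating scale alone and a gain in tested knowledge would support quite different conclusions. If the rule is chosen after the results are known, a reader cannot tell what error rate stands behind a statement that the programme works.

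**Working it through.** **Inputs from the article.** Two-sided alpha 0.05; power 0.80; d = 0.45; 77 per arm; three primary outcomes; assessments at T0 (pre-test), T1 (post-test) and T2 (follow-up).

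**Inputs not in the article, so assumed.** Correlation between outcomes 0 to 0.9; correlation between T1 and T2 test statistics 0.5 to 0.7; pre-post correlation r = 0.5 where ANCOVA is credited; d = 0.45 for every outcome, on the unadjusted SD.

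**1. The article's own figure.** n per arm = 2(z₀.₉₇₅ + z₀.₈₀)²/d² = 2(1.960 + 0.842)²/0.45² = 77.5, so 78 per arm or 156 in total. The stated 154 is within 2 participants. At 77 per arm, power is 0.797 by the normal approximation and 0.792 by the noncentral t. The 154 is therefore sound for one unadjusted comparison. By the same formula:
- at alpha 0.05/3 (Bonferroni over three outcomes), 104 per arm, 208 in total;
- for all three significant at 0.05 with independent outcomes, power per outcome must be 0.80^(1/3) = 0.928, giving 116 per arm, 232 in total.

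So 154 was not derived from either of these rules without credit for baseline adjustment.

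**2. Any one of three outcomes suffices, each at 0.05, one time point.** With independent outcomes, familywise error = 1 − 0.95³ = 0.143. Simulating equicorrelated normal test statistics:

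| Outcome correlation | Familywise error |
|---|---|
| 0 | 0.143 |
| 0.5 | 0.126 |
| 0.7 | 0.11 |
| 0.9 | 0.083 |

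**3. The same rule over T1 and T2 (six tests).** With a between-time correlation of 0.5 to 0.7, simulated familywise error runs from about 0.25 (outcome correlation 0) down to about 0.14 (outcome correlation 0.9).

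**4. All three outcomes must succeed, each at 0.05, one time point.** Type I error does not exceed 0.05. Joint power at 77 per arm follows from an expected test statistic of 0.45 × √(77/2) = 2.79 without baseline adjustment, or 2.79/√(1 − 0.5²) = 3.22 with ANCOVA at r = 0.5:

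| Outcome correlation | Unadjusted | ANCOVA, r = 0.5 |
|---|---|---|
| 0 | 0.51 | 0.72 |
| 0.5 | 0.61 | 0.78 |
| 0.7 | 0.65 | 0.81 |
| 0.9 | 0.72 | 0.85 |

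**5. Power per outcome at the first Holm step (alpha 0.05/3 = 0.0167), 77 per arm, noncentral t.** Unadjusted: 0.645. ANCOVA at r = 0.5: 0.788.

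**The case against.** Four points can be made for the article, and each has some force.

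*The 0.05 per test is inferred.* True. The only alpha belongs to the sample size calculation. The inference is reasonable, because no other level appears and 154 fits an unadjusted test, but it has to be stated as an inference.

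*A condensed article may leave multiplicity to a fuller plan.* Also true, and silence alone would not be a finding. What remains is that the article fixes 154 from one unnamed comparison and then presents three primary outcomes. A later rule would settle the decision, but the stated power would still need to be restated for it.

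*The three outcomes may be three separate claims.* On that reading 0.05 and 0.80 are right for each outcome at one time point. It would be wrong to say that the pair holds under no reading. It does not extend to one overall conclusion, and the article still does not say which time point carries each claim.

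*ANCOVA adds power.* It does, and the article says so, though the sample size takes no credit for it. Quoting 0.51–0.72 alone for an all-three rule would be one-sided. At r = 0.5 the figure is 0.72–0.85, which straddles 0.80.

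A reader might go further and infer that the programme can be declared effective on any one of nine significant tests. The document does not support this. It presents the ANCOVA contrasts as a possible analysis, with hierarchical modelling as the alternative, so nine tests are one option and not a fixed family. Nowhere does it say that one positive result is enough. The wording of the aims leans, if anything, towards requiring improvement in both knowledge and self-confidence.

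**Conclusion.** The concern stands in a limited form and should be fixed. The arithmetic behind 154 is right; what its alpha and power refer to is left open. They hold for each outcome as a separate claim at one time point, and not for a single verdict on effectiveness.

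The size depends on the rule adopted. Under an any-one rule at an inferred 0.05 per outcome, error is about 8–14% at one time point and 14–25% over T1 and T2. Under an all-three rule error is controlled, and the open question is power: clearly short of 0.80 without baseline adjustment, and not assured with it. The direction under the any-one rule holds over the whole range of outcome correlations examined. The power under the all-three rule turns on the pre-post correlation, which the article does not give. That correlation may be lower for actual knowledge, because participants see two new cases at each assessment.

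**What to change.** In the statistical analysis section:
- Name T1 as the primary time point. The Assessments section already stresses that this assessment should follow website access promptly.
- Test the three primary outcomes at T1 with Holm's procedure at a familywise two-sided 0.05.
- Label T2 and the post-to-follow-up contrast secondary.

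An all-three rule or a fixed testing order would serve equally well, provided that it is chosen before the data are examined and power is restated to match.

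In the sample size section, state power at 77 per arm and d = 0.45 as about 0.65 per outcome at the first Holm step without baseline adjustment, or about 0.79 with ANCOVA if the pre-post correlation is 0.5. Mark that correlation as an assumption, with the caution on actual knowledge.

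The cost is about a paragraph of text and a less favourable stated power. No extra recruitment is needed.

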### Randomization

Every time a participant completes the baseline assessment, the researcher sends an e-mail to an independent external data manager to randomize this person to one of the two groups. The data manager uses block randomization in IBM Statistics SPSS and reports the outcome to the researcher by e-mail.

### Assessments

Within four days after completing the baseline assessment the participants receive an e-mail from the researcher regarding the group they are assigned to and are informed on which day they will receive the second assessment. Additional to this information, those in the experimental group receive a personal username and password to log in to the website *Mental Health Online* and are informed regarding the exact period (14 days) during which they have access to the website. An instruction to the website is also attached to this e-mail.

Four weeks after completing the first assessment participants from both groups receive the second assessment (post-test), and 12 weeks after completing the second assessment the third assessment (follow-up) will be sent to the participants.

The three assessments which consist of the three questionnaires (including the evaluation questionnaire) are sent to the participants as a complete package online, and data collection is performed online.

Participants from the experimental group will regain access to the modules and additional information on the website after completing the second assessment until one week prior to the last assessment. This way, participants from the experimental group can return to the website to refresh their knowledge, follow modules they did not follow during the 14 days they had access to the website, and use the additional information and the online discussion board on the website. The reason behind making the website accessible during this relatively long period has to do with the online character of the program. By providing the modules online, we can create a low threshold to the training which is accessible to gatekeepers 24/7.

After completing each assessment, the researcher sends a personal email to the participant in which information regarding the next assessment is provided. Furthermore, participants will receive reminders by email to complete the assessments. Participants will receive weekly reminders for the first and the third assessment. However, since it is important that the second assessment is completed immediately after accessing the website, reminders to finalize this assessment will be sent every other day if necessary. After completing the third and final assessment, participants from the waitlist control group will receive an email with a personal username and password for the website, including instructions for the website. The trial flowchart of this study is given in Figure 
1.

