**Methods/Design:**

A randomized controlled trial will be carried out among 154 gatekeepers. After completing the first assessment (pre-test), participants will be randomly assigned to either the experimental group or the waitlist control group. One week after completing the first assessment the experimental group will have access to the website *Mental Health Online* containing the eight e-learning modules and additional information on adolescent suicide prevention. Participants in both conditions will be assessed 4 weeks after completing the first assessment (post-test), and 12 weeks after completing the post-test (follow-up). At post-test, participants from the experimental group are asked to complete an evaluation questionnaire on the modules. The waitlist control group will have access to the modules and additional information on the website after completing the follow-up assessment.

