## Methods

### Study design

This study is a randomized controlled trial with two arms: an experimental group and a waitlist control group. Participants from both groups will complete three assessments: at baseline (pre-test, T₀), four weeks after completing the first assessment (post-test, T₁), and 12 weeks after T₁ (follow-up, T₂). Participants will be assigned to one of the two groups (experimental or waitlist control group) after completing the baseline assessment. The difference between the two groups is that participants in the experimental group will have access to the e-learning modules and additional information on the website *Mental Health Online* (http://www.MentalHealthOnline.nl) seven days after completing the first assessment, while participants in the waitlist control group have to wait until the follow-up assessment is completed.

The assessments consist of three questionnaires which measure the perceived knowledge, the perceived self-confidence, and the actual knowledge of participants in both groups regarding adolescent suicidality. By comparing the questionnaire information obtained from the two groups during the three assessments it is tested whether the perceived knowledge, the perceived self-confidence, and the actual knowledge of participants in the experimental group improves more than in participants in the waitlist control group after gaining access to the e-learning modules and additional information on the website.

The study protocol for *Mental Health Online* has been approved by the Medical Ethics Committee of the VU University Medical Centre Amsterdam (registration number 2009/328).

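### Follow-up (T2) is timed from completion of the post-test (T1), so a randomised participant who does not complete T1 has no stated T2 date and may be lost to both post-baseline assessments

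*Protocol article*

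**What the plan says.** The Assessments section of the protocol article sets the two post-baseline assessments by different anchors.

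- **T1** is counted from baseline: "Four weeks after completing the first assessment participants from both groups receive the second assessment (post-test". Baseline is complete before anyone is randomised, so every randomised participant has a T1 date.
- **T2** is counted from the participant's own T1 response: "12 weeks after completing the second assessment the third assessment (follow-up) will be sent to the participants". The abstract agrees: "12 weeks after completing the post-test (follow-up". The Study design section is looser, with "12 weeks after T₁ (follow-up, T₂", and does not say whether sending or completing T1 starts the clock.

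Notice of what comes next also depends on completing the previous step: "After completing each assessment, the researcher sends a personal email to the participant in which information regarding the next assessment is provided".

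T1 has intensive chasing: "reminders to finalize this assessment will be sent every other day if necessary". The first and third assessments have weekly reminders. The article gives no closing date for T1 and no fallback T2 date.

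The Statistical analysis plan section states: "All analyses will be carried out on intention-to-treat sample". It offers ANCOVA with multiple imputation, or a hierarchical linear model that assumes data are missing at random.

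**The concern.** Intention-to-treat analysis needs outcome data sought from everyone randomised, whatever they did earlier in the trial. Here the T2 invitation depends on a post-randomisation behaviour. If the rule is applied as written, a participant who skips T1 but would have answered three months later is not asked, and a gap at one visit becomes a gap at both.

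Neither analysis method repairs that. For such a person the pre-test is the only outcome measurement. Module-use tracking adds something, but before T2 only in the experimental arm. A T2 answer, had it been requested, would be a real observation at T2 and would also inform the imputed T1 value. People who ignore T1 are also those for whom missing at random is hardest to defend.

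**Working it through.** **1. Does the sample size contain a margin?** Inputs from the Sample size section: d = 0.45, two-sided α = 0.05, power 0.80, 77 per arm.

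- n per arm = 2 × ((1.960 + 0.842) / 0.45)² = 77.5, or 78 after rounding up (156 in total). The stated 154 is reproduced to within 2 participants.
- Power at 77 per arm = Φ(0.45 × √(77/2) − 1.960) = Φ(0.832) = 79.7% (79.2% with the t distribution).

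The 154 is therefore the number needed with complete data, and it includes no attrition allowance.

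**2. How many T2 records are at stake?** The article gives no T1 non-response rate and no likelihood that a T1 non-responder would answer T2. Both are assumptions here.

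Records not collected = T1 non-response × 154 × share who would answer T2. With a share of one half:

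- 5%: 0.05 × 154 × 0.5 = 3.9
- 15%: 0.15 × 154 × 0.5 = 11.6 (7.5% of 154)
- 30%: 0.30 × 154 × 0.5 = 23.1

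**3. What does that do to power at T2?** The same formula is used on complete cases. n per arm is 77 × (1 − m) if T1 non-completers are not sent T2, and 77 × (1 − m(1 − r)) if they are and a fraction r answer. For simplicity this assumes no other T2 loss and equal loss in both arms.

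| Assumed T1 non-completion m | Not sent T2 | Sent T2, r = 25% to 50% |
|---|---|---|
| 10% | 69.3 per arm, 75.5% | 76.6% to 77.7% |
| 20% | 61.6 per arm, 70.5% | 73.0% to 75.5% |
| 30% | 53.9 per arm, 64.7% | 69.1% to 73.0% |

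The gain runs from 1.1 points (76.6 − 75.5) to 8.3 points (73.0 − 64.7). These figures ignore the precision that the pre-test covariate would add. They show the size of the effect and do not forecast the trial's power.

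**4. Timing for late completers.** Day of T2 from baseline = 28 + T1 delay + 84. A delay of 0, 14 or 28 days gives day 112, 126 or 140. The interval from T1 to T2 stays at 84 days in each case.

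**The case against.** The strongest reply is that the article describes the schedule for a participant who follows it. It says that both groups are assessed at all three points and commits to intention-to-treat. What happens after a missed questionnaire may be settled in the full protocol, which is not shown. This stands against one tempting reading, that T1 non-completers never receive T2: no sentence says so. It does not dispose of the point. The article goes beyond silence by fixing a trigger, stated in two places, and that trigger yields no date for these people.

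Counting from T1 completion also has a purpose. It holds the T1-to-T2 interval constant, which suits the planned post-test to follow-up comparison. It also stabilises the renewed website access, since those in the intervention arm "will regain access to the modules and additional information on the website after completing the second assessment until one week prior to the last assessment". Moving everyone to week 16 would shorten both for late completers. This stands: the later T2 of a late T1 completer is a trade-off and not an error.

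The frequent T1 reminders aim at exactly this risk. They lower it, but those who still do not respond remain without a T2 date.

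A reader might also infer that T1 loss, or time since randomisation at T2, will differ by arm. The documents do not support a direction. The experimental arm has an extra 34-question evaluation at T1, which may deter, and renewed access on completing T1, which may encourage. The waitlist arm has its own incentive, access after the follow-up.

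**Conclusion.** The concern holds in a limited form. The stated trigger leaves a randomised T1 non-completer without a T2 date. This works against the intention-to-treat commitment, in a trial whose sample size has no margin for loss. The T2 answers at risk are ones that imputation or a mixed model cannot replace.

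The size is not known from the document. The range of about 4 to 23 of 154 T2 records rests wholly on the assumed 5% to 30% T1 non-response and on half of those people answering T2. At low non-response the effect on power is only 1 to 2 points. Actual exclusion of T1 non-completers, bias between arms, and harm from the later T2 of late completers are not established.

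**What to change.** State in the Assessments section that T2 is sent, with the same weekly reminders, to every randomised participant whether or not T1 was completed. Then:

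- For those who complete T1 by a stated cut-off, keep 12 weeks after T1 completion if the constant interval and access window are wanted.
- For anyone who has not completed T1 by that cut-off, send T2 at week 16 from baseline (4 + 12).
- Record the actual completion dates of T1 and T2.
- Bring the Study design wording and the abstract into line with this rule.

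The cost is a changed e-mail trigger and a few more messages. T2 will have two anchors, so time since baseline will not be uniform. A person who completes T1 after the cut-off will have an interval shorter than 12 weeks, and the protocol should say how that person's assessment and access dates fit together.

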### Secondary outcome measures

The secondary outcome is the satisfaction of the gatekeepers regarding the design of the e-learning modules. During the second assessment, participants from the experimental group are asked to complete a short evaluation questionnaire. In this questionnaire, characteristics of the e-learning modules are evaluated using 34 questions on expectations (2 items), relevance (2 items), design (5 items), interaction (2 items), cases and quizzes (11 items), overall satisfaction (6 items), website (5 items), and final commentary (1 item).

The questions are answered using the following format: a four-point Likert scale (17 items), multiple choice (3 items), rating (2 items), yes/no (4 items), and multiple responses (1 item). Seven of the questions are optional open questions which give the participant the opportunity to elaborate on their previous answers. Based on the answers the e-learning modules will be adjusted for implementation.

In addition, an attempt is made to improve the skills of the gatekeepers by providing them with frameworks, tips, and information in the e-learning modules. Due to privacy issues it is not possible to measure changes in this particular area as monitoring each gatekeeper, including an overview of false and correct referrals, would be required. However, participants from the experimental group are asked to rate several general statements on a four-point Likert scale as part of the evaluation questionnaire. One of these statements concerns the perceived gain in skills (‘By following the e-learning modules I have gained more skills in interaction with suicidal adolescents’). By asking the participants to rate this particular statement an overall indication of the impact of the e-learning modules on the skills of the participants can be obtained.

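### Completing the follow-up assessment earns website access in the waitlist arm only, which risks higher follow-up loss in the experimental arm

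*Protocol article*

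**What the plan says.** The access rules are in the Study design and Assessments sections of the protocol article.

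- **Experimental arm, before T1.** Participants "are informed regarding the exact period (14 days) during which they have access to the website". This first period does not depend on completing any later assessment.
- **Experimental arm, between T1 and T2.** They "will regain access to the modules and additional information on the website after completing the second assessment until one week prior to the last assessment". The article describes no access after that.
- **Waitlist arm.** Under Study design, "participants in the waitlist control group have to wait until the follow-up assessment is completed". Under Assessments, "After completing the third and final assessment, participants from the waitlist control group will receive an email with a personal username and password".
- **Timing of T2, both arms.** "12 weeks after completing the second assessment the third assessment (follow-up) will be sent to the participants".
- **Knowledge of allocation.** Participants are told their group by e-mail within four days of completing the baseline assessment.
- **Reminders.** They go out every other day for T1 and weekly for T2, with no stated difference between arms.
- **Analysis.** The Statistical analysis plan section offers ANCOVA with multiple imputation or, alternatively, HLM under missing at random. It adds: "All analyses will be carried out on intention-to-treat sample".

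**The concern.** When the T2 invitation arrives, a waitlist participant who answers receives the training for the first time. An experimental participant lost access a week earlier and, on the text, gets nothing further by answering. Both know their arm. The immediate reason to respond at the final time point is therefore unequal by design.

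Unequal loss does not bias the comparison by itself. Bias arises if those who leave would have scored differently from those who stay, in a way the observed data do not explain. Experimental participants who took little from the modules have the least other reason to return at T2, and they may also be the ones with lower scores. If so, the remaining experimental participants would look better than the full randomised group, and the T2 effect on perceived knowledge, self-confidence and actual knowledge would be overstated. Analysing by intention to treat keeps participants in their allocated arm but does not supply the scores they did not give.

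**Working it through.** **1. Incentives at T2, side by side**

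| | Experimental | Waitlist |
|---|---|---|
| Access in the week before T2 | closed | never opened |
| Access gained by completing T2 | none described | first access to the site |
| Reminders | weekly | weekly |
| Knows own arm | yes | yes |

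The only stated difference in what completing T2 brings is the login for the waitlist arm.

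**2. The plan's own figure**

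Inputs from the Sample size section: d = 0.45, two-sided alpha 0.05, power 0.80, 77 per arm.

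n per arm = 2 × (1.960 + 0.842)² / 0.45² = 77.5. This rounds up to 78, within one participant per arm of the stated 77. Power at 77 per arm is 0.797. The stated figure is reproduced, and it contains no allowance for loss.

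**3. Shift in a completer-only difference**

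The article gives no drop-out rates, so these inputs are assumptions: a gap in loss of 10 or 20 percentage points, and drop-outs whose mean lies g = 0.2 or 0.5 SD below that of completers, with g the same in both arms.

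With a proportion p lost, the full-arm mean is (1 − p) × C + p × (C − g) = C − p × g, where C is the completer mean. The completer mean therefore exceeds the full-arm mean by p × g, and the between-arm difference shifts by

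(p_E − p_C) × g.

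| Gap p_E − p_C | g = 0.2 | g = 0.5 |
|---|---|---|
| 0.10 | 0.02 SD | 0.05 SD |
| 0.20 | 0.04 SD | 0.10 SD |

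As a share of 0.45, the range runs from 0.02/0.45 = 4% to 0.10/0.45 = 22%. The shift favours the experimental arm if that arm loses more, and reverses if the waitlist arm does. With equal loss in both arms it is zero. All of these values are before pre-test adjustment, use of T1 scores or imputation.

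**4. Power**

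With 30% loss in one arm and 10% in the other, 53.9 and 69.3 participants remain and power is 0.698. With 20% in each arm, the same total loss, it is 0.705. Imbalance itself costs little power, so the issue is possible bias.

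**5. Can the same be said of T1?**

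Completing T1 reopens the site for the experimental arm for about 12 − 1 = 11 weeks. Two features pull the other way. T2 is timed from completion of T1, so a waitlist participant must complete T1 to move towards access. At T1 the experimental arm also has an extra task: "During the second assessment, participants from the experimental group are asked to complete a short evaluation questionnaire", which has 34 questions. The article gives no means of weighing these against each other, so the net direction at T1 is undetermined.

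**The case against.** The strongest reply is that this is an ordinary waitlist design with sound missing-data methods. Controls must wait until follow-up is over, reminders are described without distinction by arm, and no drop-out rates are given from which to infer a problem. HLM uses observed T1 scores when T2 is missing, and multiple imputation can do so. User tracking records module use in both periods, and the T1 evaluation questionnaire records satisfaction, so both could inform imputation. Which variables enter the imputation is detail an article may leave to a fuller document.

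Much of this stands. It rules out several stronger readings that a reader might infer:

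- **That unequal drop-out is built in.** The text fixes unequal incentives. Whether response follows them is not known.
- **That incentives run in opposite directions at T1 and T2.** This would require a waitlist participant to gain nothing from completing T1, which the timing of T2 contradicts.
- **That experimental access is never restored.** The article is silent on access after T2. It is condensed, and its flowchart is not available here.
- **That the missing-at-random methods fail.** They correct loss explained by observed data. Loss tied to unobserved T2 scores is possible but not shown.
- **That a single bias figure can be given.** Any such figure rests on assumed rates and an assumed link between response and outcome.

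The objection does not remove the stated asymmetry at T2. Good missing-data methods are a second line of defence, and preventing the loss is preferable when it costs almost nothing.

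**Conclusion.** The point holds as a risk at T2. As written, completing the final assessment is rewarded with access in the waitlist arm only, and participants know which arm they are in. Higher follow-up loss in the experimental arm is the more plausible direction, but that is an inference.

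The illustrative size is 0.02 to 0.10 SD in a completer-only comparison, or 4% to 22% of the assumed effect. This rests on loss gaps of 10 to 20 points, drop-outs 0.2 to 0.5 SD below completers, and the same g in both arms. It is not an estimate of the bias in the planned analysis, which could be smaller. No conclusion about T1 is supported. The change is a nearly free improvement and does not correct an error that invalidates the comparison.

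**What to change.** Offer both arms the same open website access on completing T2: restored access for the experimental arm and first access for the waitlist arm. Announce it in the same terms to both arms in the allocation e-mail and again in the T2 invitation. For participants already allocated, the T2 invitation can carry it. If post-T2 access for the experimental arm is already intended, stating it in those e-mails is enough.

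Leave the T1 access rule as it is. Reopening the site by date instead of on completion would remove an incentive to complete T1, and anyone answering late would take the post-test after renewed exposure.

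The cost is e-mail wording and account dates on a site that must be open to waitlist participants after T2 anyway. T2 is the last assessment, so the added access cannot influence any outcome, and the waitlist arm's incentive is unchanged.
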